## Assignment of interventions: blinding

### Who will be blinded {17a}

Participants will be blinded to group allocation. Participants allocated to the sham group will receive stimulation at motor threshold intensity for 1 min, followed by a gradual return to no stimulation to mimic the initial sensation of stimulation followed by the acclimation to cutaneous stimulation. The study personnel performing locomotor training, clinical assessments, and data analysis will be blinded to the group allocation. Because each participant’s study code is not linked to the group assignment, those who perform data analysis cannot recognize the study group of a participant.

### Procedure for unblinding if needed {17b}

Staff members who perform the thoracolumbar electrical stimulation and the biostatistician who performs the allocation are not blinded. We do not anticipate any requirement for unblinding but if required, the investigators will have access to group allocations and any unblinding will be reported. Data will be unblinded when data analysis is completed and statistical tests between study groups need to be performed.

## Data collection and management

### Plans for assessment and collection of outcomes {18a}

Neurophysiological biomarkers and clinical outcome assessments at baseline and after 40 sessions of therapy are taken by the same investigator while using the same equipment and settings to ensure consistency and repeatability of recordings and assessments. Laboratory tests/experiments involve recordings of muscle action potentials following brain and/or peripheral nerve stimulation via surface EMG electrodes based on consensus standards for electrophysiological recordings. Consistency of recordings between sessions is ensured from using similar anatomical landmarks, detailed notes on thresholds, amplitude, and behavior of action potentials at a wide variety of stimulation intensities. Data from each participant is checked for completeness through validity checks.

### Plans to promote participant retention and complete follow-up {18b}

Explanation of the study, including possible benefits, increases recruitment and retention in randomized clinical trials [92]. It is a standard procedure in our lab to describe the research study in detail and answer all questions that a participant may have. The eligible participant is always encouraged to ask questions about the procedures and no information is withheld. During the discussion, participants are informed of the expectation that they can commit to traveling to either site for training/intervention sessions at least 4 times per week for up to 3 months. If the participant or study team perceives difficulty in meeting these expectations, then enrollment is deferred. After the consent form is signed, we develop a calendar for each participant based on the time needed to come to the lab, job obligations, or other commitments. The calendar includes all experimental and training sessions for the total duration of the study and is emailed to the participant. We also make use of electronic calendar invitations for reminders, and emails or texts before each visit depending on the participant. These procedures can decrease some common reasons for dropouts in clinical trials such as fear and anxiety during the study, schedule conflicts, forgetting visits, lack of appreciation, and misunderstood expectations. Thus, the procedures that we follow — explaining the importance of participation, setting expectations, reminders of visits, accommodation of the schedule, and promptly responding to inquiries — are expected to contribute to better retention of participants.

### Data management {19}

All participants are given a unique identifying number that is used on all clinical and experimental data for that participant. Clinical data in paper format are kept in a locked file cabinet, while clinical data entered directly from the source documents along with the experimental data are saved with a unique code in password-protected computers.

### Confidentiality {27}

Participant confidentiality is strictly held in trust by all investigators and staff. The study protocol, documentation, data, and all other information generated are held in strict confidence. No information concerning the study or the data are released to any unauthorized third party without prior written approval of the sponsor. Participants are consented individually and participate one at a time, which limits the opportunity for others to become aware of the participant’s participation or responses. All individually identifiable data is protected and only accessible to research staff.

All participants are identified by a study code upon randomization without any identifiable information. The study code is used to save all data in digital forms and written documents, and when data are reported either in a conference or in a research article. Furthermore, signed consent forms and all documents that can identify a participant are kept separate from all forms related to experimental procedures like subject data sheets or post-study questionnaires.

Informed consent documents and medical records: Informed consent is taken in a private, quiet room, and the investigator obtaining informed consent explains procedures thoroughly while asking if the participant has questions at several times during the process. Informed consent documents and medical records are kept separately from all other study data in a locked cabinet at both performance sites. The key is stored in a locked room separate from any of the participants’ data. Only authorized personnel have access to these cabinets.

Email/phone screening information: Information collected during the email or phone screen including names and contact information are entered into a secure database or locked in file cabinets in one of the labs. Once the participant has consented, documents containing protected health information or personally identifiable information are always kept separately from study data linked to the participant’s study code.

### Plans for collection, laboratory evaluation, and storage of biological specimens for genetic or molecular analysis in this trial/future use {33}

None. Not applicable. No biological specimens are collected for research purposes.

## Statistical methods

### Statistical methods for primary and secondary outcomes {20a}

For each dependent variable (primary and/or secondary outcome), descriptive statistics including frequencies and percentages for categorical variables and means and percentile distributions for continuous variables to examine the distribution of outcomes and describe the study population are performed.

We will group each dependent variable based on the time of testing (before and after the intervention) and the subject group (2 experimental, 1 sham). A two-way mixed analysis of variance (ANOVA) along with Bonferroni post hoc* t-*tests [93] at 2 3 levels (2: time, 3: groups) to test the main and interaction effects among subject groups and time will be performed separately for each outcome. Furthermore, repeated measures analysis of covariance (ANCOVA) will be performed for each outcome separately with gender, age, level of SCI, and clinically evaluated baseline walking function as separate covariates. Outcomes will not be analyzed based on SCI severity because the ISNCSCI scale does not correlate with improvements in walking ability [3], while age is considered one of the predictors of ambulation in SCI [94].

Mixed regression methods and analysis of slope and threshold of correlation will be used to establish the relationship between the ability to stand and walk, quality of life, and changes in primary outcomes (neurophysiological biomarkers). We will use an identity or log link based on the data distribution.

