### Objectives {7}

The overall objective of this mechanistic randomized clinical trial is to use transspinal stimulation over the thoracolumbar enlargement, the spinal location of leg motor circuits, to prime locomotor training and ultimately improve the ability to stand and walk in individuals with chronic incomplete SCI. We hypothesize that non-invasive thoracolumbar transspinal stimulation administered before locomotor training increases neuronal responsiveness over multiple spinal segments, mechanistically reflected by increased responses to motor cortex stimulation, and improved phase-dependent modulation of spinal reflexes during walking. Because transspinal stimulation facilitates anti-gravity neuronal circuits, we further hypothesize that transspinal stimulation delivered while participants stand will augment gains compared to delivery in the supine position. To meet our overall objective, 45 individuals with incomplete SCI will undergo 40 sessions of BWS step training primed with 30 Hz transspinal stimulation. Participants are randomized to receive transspinal stimulation during standing (active or sham) or while supine (active).

Our *specific objective 1* determines whether priming locomotor training with transspinal stimulation strengthens corticomotoneuronal connectivity through posture-dependent corticospinal neuroplasticity, as reflected by increased MEP amplitudes and phase-dependent MEP amplitude modulation during stepping. We hypothesize that active but not sham transspinal stimulation delivered during standing increases MEP amplitudes and improves phase-dependent MEP amplitude modulation during stepping. We further hypothesize that transspinal stimulation delivered while supine increases MEP amplitudes but does not induce phase-dependent MEP amplitude modulation during stepping.

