### Outcomes {12}

#### Primary outcomes

The primary outcomes are neurophysiological biomarkers that accurately probe corticospinal and spinal neuroplasticity (at presynaptic and postsynaptic motoneuron levels):Corticospinal neuronal excitability:

We establish the active MEP threshold that corresponds to the intensity that evokes 10 responses of at least 50 mV following 20 1-ms transcranial magnetic stimulation (TMS) pulses in seated subjects. Then, the soleus MEP recruitment input–output curve is assembled while maintaining small-amplitude contractions. During BWS-assisted stepping, MEPs are recorded at 1.3 times the right soleus MEP active threshold randomly at different phases of the step cycle (divided into 16 equal bins or time windows) based on the signal from the right foot switch. During stepping, MEPs are collected before and after intervention using Lokomat settings matched to the baseline, while an effort is made to record MEPs using Lokomat settings matched to those of the last training session. This establishes changes at matched settings and adaptations during more demanding stepping conditions. MEPs recorded at different stimulation intensities (recruitment curve) are measured as peak-to-peak amplitude and normalized to the soleus maximal M-wave (Mmax) evoked by posterior tibial nerve stimulation to counteract differences in muscle fiber composition across subjects. Stimulation intensities are normalized to the intensity corresponding to the 50% of the MEPmax amplitude, estimated based on the sigmoid function fit to the data. For the participants who have obtainable soleus MEPs at baseline, the main outcomes from this experiment are the MEPmax from the MEP recruitment curves and the MEP amplitude at the mid-stance and mid-swing phases before and after the intervention.2)Spinal neuronal excitability:*2a) Soleus H-reflex rate-dependent (or homosynaptic) depression*: To assess restoration of homosynaptic depression exerted at the synapses between muscle spindle primary Ia afferents and alpha motoneurons, soleus H-reflexes following posterior tibial nerve stimulation at the popliteal fossa with a 1-ms pulse are recorded from seated subjects at different frequencies (1.0, 0.33, 0.2, 0.125, and 0.1 Hz). Homosynaptic depression is greatest at 1.0 Hz and fully recovers at 0.125 and 0.1 Hz [69]. Homosynaptic depression cannot be recorded during stepping because it is abolished by strong spinal inhibitory circuits and efferent activity. The main outcome measure from this neurophysiological biomarker is the soleus H-reflex 1.0/0.1 Hz ratio [70].*2b) Soleus H-reflex depression by antagonistic nerve stimulation*: To examine the restoration of reciprocal inhibitory actions on antagonistic alpha motoneurons, the soleus H-reflex is conditioned by common peroneal nerve (CPN) stimulation at conditioning-test (C-T) intervals of 0, 1, 2, 3 and 4 ms, with subjects seated [71–75]. Reproducible CPN conditioning stimulation is ensured by using a stable, small-amplitude TA M-wave and similar soleus M-wave amplitudes under control and conditioning stimulations. Soleus H-reflexes are measured as peak-to-peak amplitude, accepted for M-waves ranging from 2 to 8% of the maximal M-wave (Mmax), and normalized to the Mmax. The main outcome is the amplitude of the conditioned soleus H-reflex as a percentage of the control H-reflex. The C-T interval for which reciprocal inhibition is present or reciprocal facilitation is the smallest is further investigated during BWS-assisted stepping. The main outcomes are the conditioned H-reflex at rest and during the stance and swing phases of BWS-assisted stepping, which both reflect the amount of reciprocal inhibition.*2c) Control and conditioned soleus H-reflexes during stepping*: During standing with BWS as needed, the soleus H-reflex and M-wave recruitment curves are assembled. Then, each participant steps with the assistance of the Lokomat, and soleus H-reflexes are recorded under control conditions and following CPN conditioning stimulation randomly across 16 equal time bins into which each step cycle is divided based on the signal from the foot switch [75]. The tibial nerve stimulation intensity is adjusted in real-time online to evoke H-reflexes such that their corresponding M-waves are 2–8% of the Mmax evoked 80 ms after the test H-reflex at each bin (Fig. 3). Control and conditioned soleus H-reflexes during stepping are collected before (baseline) and 1–2 days after completion of all 40 intervention sessions at Lokomat settings matched to baseline and the last training session. This approach determines changes at matched settings and reflex adaptation at more demanding settings [76]. During stepping, soleus H-reflexes are measured as peak-to-peak amplitude, accepted for M-waves ranging from 2 to 8% of the Mmax, normalized to the Mmax, and averaged for each bin of the step cycle. The main outcome is the control and conditioned soleus H-reflex amplitude normalized to the Mmax at mid-stance and mid-swing phases.

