#### Secondary outcomes

The secondary outcomes include the International Standards for Neurological Classification of SCI (ISNCSCI) sensory and motor scores, temperature sensation, proprioceptive sensation, ability to stand and walk, and autonomic function. Standing and balance ability is evaluated with the Berg Balance Scale [77, 78] and BEST tests [79]. Walking capacity is tested with the 2-min and 10-m walking tests [80]. A combination of validated questionnaires related to bladder, bowel, and sexual function are used to assess autonomic function [81–87].

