## Oversight and monitoring

### Composition of the coordinating center and trial steering committee {5d}

The principal investigators (PIs) of this clinical trial are PI # 1, [name], PT, MBA, PhD, at the College of Staten Island, City University of New York, and PI # 2, [name], PhD, at Icahn School of Medicine at Mount Sinai and James J. Peters Veterans Affairs Medical Research Center (JJPVAMC). PI # 1 performs along with her research team at the Klab4Recovery all neurophysiological recordings before and after training for all study participants of the clinical trial to ensure consistent experimental procedures for all neurophysiological recordings. PI # 1 also leads the implementation of transspinal stimulation and locomotor training interventions, as well as the clinical assessments before and after training for study participants at Klab4Recovery. PI # 2 leads the implementation of transspinal stimulation and locomotor training interventions as well as the clinical assessments before and after training for study participants at JJPVAMC. Both PIs ensure that locomotor training and transspinal stimulation are implemented equivalently at both sites. The trial steering committee is composed of the PIs and dedicated research staff.

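### Free improvement: the primary outcomes are not adjusted for their own baseline and the deciding test per outcome is not named; one baseline-adjusted primary model would gain precision and settle the choice

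*Protocol article*

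**What the plan says.** The section on statistical methods for primary and secondary outcomes fixes two models.

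- The first is "A two-way mixed analysis of variance (ANOVA) along with Bonferroni post hoc" comparisons. Its stated purpose is "to test the main and interaction effects among subject groups and time will be performed separately for each outcome". The pre-intervention value enters as the first level of the time factor, that is, as a response.
- The second is added to it: "repeated measures analysis of covariance (ANCOVA) will be performed for each outcome separately". The variables listed for this model are "gender, age, level of SCI, and clinically evaluated baseline walking function as separate covariates". The outcome's own pre-intervention value is not on that list.

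The outcomes section states: "The primary outcomes are neurophysiological biomarkers that accurately probe corticospinal and spinal neuroplasticity". These are MEP and soleus H-reflex measures, and the participant timeline has them recorded at baseline visits before the first treatment session, so the missing covariate is already collected.

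The methods section does not name one effect within the ANOVA, or one of the two models, as decisive. The sample-size section sizes Aim 1 on a within-between interaction, but cites one-way ANOVAs for the Aim 2 outcomes.

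**The concern.** There are two separate issues.

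**Precision.** In a randomised design with one pre and one post measurement, the group-by-time interaction is the same test as a one-way ANOVA of change scores. A change score subtracts the whole baseline value, which over-corrects whenever the pre-post correlation is below 1. Regression on baseline removes only the part that predicts the post value. With 15 participants per arm, giving up precision that costs nothing to keep is worth avoiding.

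**Choice of test.** Each outcome yields a time effect, a group effect and an interaction, and then one or more ANCOVA results. Only the interaction, or its covariate-adjusted version, answers the randomised question. The time effect includes the locomotor training that all arms receive, and the group effect averages in values measured before treatment. With no ranking in the methods section, which p-value carries the conclusion could be settled after the results are seen.

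**Working it through.** **Inputs from the article.** Three arms in equal ratio, 45 enrolled (15 per arm); two measurement times; alpha 0.05, power 0.80; Aim 1 mean difference 148.05 and pooled SD 206.8, given as d = 0.71; stated Aim 1 total 24.

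**Inputs not in the article (assumptions).** The pre-post correlation rho, taken over 0.3 to 0.9; equal pre and post variance s²; covariate slopes for the type I error check.

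**1. The plan's own figure.** For the group-by-time interaction with m = 2 times, lambda = f² × N × m / (1 - rho), with 2 and N - 3 degrees of freedom. Take f = d/2 = 0.355 and rho = 0.5:

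lambda = 0.355² × 24 × 2 / 0.5 = 12.10 on 2 and 21 df, giving power 0.833.

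With N in multiples of 3, 24 is the smallest total that reaches 0.80, so the stated figure reproduces. With rho = 0.3 the same formula gives 30, and with rho = 0.7 it gives 15. The match is only weak evidence that rho = 0.5 was used: at rho = 0.5, lambda reduces to d² × N, which is also what a one-way ANOVA gives if d is entered as f.

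**2. Residual variance of the two analyses.**

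- Change score (the planned interaction): s² + s² - 2 rho s² = 2(1 - rho)s²
- Post value adjusted for own baseline: (1 - rho²)s²
- Ratio, adjusted to change: (1 - rho)(1 + rho) / [2(1 - rho)] = (1 + rho)/2
- Saving: 1 - (1 + rho)/2 = (1 - rho)/2
- Extra participants the change score needs for equal precision: 2/(1 + rho) - 1

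| Assumed rho | Change, 2(1 - rho) | Adjusted, 1 - rho² | Saving | Extra participants |
|---|---|---|---|---|
| 0.3 | 1.40 | 0.91 | 35% | 54% |
| 0.5 | 1.00 | 0.75 | 25% | 33% |
| 0.7 | 0.60 | 0.51 | 15% | 18% |
| 0.8 | 0.40 | 0.36 | 10% | 11% |
| 0.9 | 0.20 | 0.19 | 5% | 5% |

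The formula ignores the degree of freedom spent on the baseline term. With 45 analysed, error df go from 45 - 3 = 42 to 41. That takes a little off the gain and is noticeable only where the gain is already small.

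**3. Unranked p-values.** Null data were simulated with 15 per arm. An error was counted if the interaction or any ANCOVA group test fell below 0.05.

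| Reading of the covariate wording | Covariates unrelated to change | Slope 0.3 on each of four standardised covariates |
|---|---|---|
| Four one-covariate ANCOVAs | about 0.06 to 0.08 | about 0.09 to 0.10 |
| One ANCOVA with four terms | about 0.06 to 0.07 | about 0.08 |

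The inflation is modest because the tests are strongly correlated. A fair summary is 6% to 10% per outcome, against a nominal 5%.

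**The case against.** The strongest reply is that nothing here is invalid. Under randomisation the interaction is a legitimate test of the arm effect, and preferring baseline adjustment is a recommendation about efficiency. That stands, and it sets the grade of this point.

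It can also be said that the intended test is inferable: Aim 1 is sized on the interaction, and the ANCOVA is introduced after the ANOVA as something further. That stands for Aim 1. It does not settle the Aim 2 outcomes, whose sample sizes cite a different test. A condensed article may leave explicit ranking to an analysis plan that is not shown. The models and covariates themselves, however, are fixed here, and the article states that no additional analyses are planned.

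A reader might infer more than the documents support:

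- **That 15% to 35% of the variance is lost.** That needs rho between 0.3 and 0.7, and the article gives no rho.
- **That no outcome is ever adjusted for its own baseline.** "Walking capacity is tested with the 2-min and 10-m walking tests", so for those secondary outcomes the baseline walking covariate may be the outcome's own baseline or a close proxy. The point is confined to the primary outcomes.
- **That site must be in the model.** It is true that "PI # 2 leads the implementation of transspinal stimulation and locomotor training interventions as well as the clinical assessments" at the second site. But one team makes all the primary neurophysiological recordings, and the randomisation section describes no stratification by site. Adding site is a preference.
- **That within-arm p-values will decide.** "We hypothesize that active but not sham transspinal stimulation delivered during standing increases MEP amplitudes" is a hypothesis and not an analysis rule; the analysis section plans a test between groups.
- **That the trial is shown to be underpowered.** The planning effects are within-group pre-post differences. Reading them as differences between arms would put a scenario into the protocol that it does not state.

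**Conclusion.** The point holds as a free improvement in precision and clarity; it is not an error that invalidates the plan. For the primary neurophysiological outcomes, own-baseline adjustment reduces residual variance by (1 - rho)/2 relative to the planned interaction, for any rho below 1 under equal pre and post variances. At rho = 0.5, the value with which the Aim 1 total reproduces but which the article does not document, that is 25%. If the biomarkers are very repeatable (rho of 0.8 to 0.9) it is only 10% to 5%.

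The missing ranking of tests carries a modest error-rate cost of about one to five percentage points per outcome. It applies only if whichever interaction or ANCOVA result is significant could be claimed, and its size rests on the assumed slopes and on the reading of *separate*.

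**What to change.** State one primary model per outcome: the post-intervention value on arm, adjusted for that outcome's own baseline, or the equivalent constrained longitudinal model. List any other covariates in that same model in advance, which also removes the ambiguity over one ANCOVA or four.

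Base conclusions on the between-arm contrasts from that model: active-standing against sham-standing, and active-standing against active-supine. Label the mixed ANOVA and any other covariate models as supportive.

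The cost is a wording change and one degree of freedom for the baseline term; no new data are needed. Because the article has data unblinded when the between-group tests are to be run, the wording should be fixed before then.
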